#### The Geriatric Depression Scale

The Geriatric Depression Scale (GDS) has been well validated and widely used in Primary Health Care research [31]. The GDS-15 will be used to limit the time imposed on participants.

#### The WHOQOL-BREF

The WHOQOL-BREF is a widely used quality of life instrument [32], which has been validated for use in the Australian population [33].

#### The Beck Depression Inventory

The Beck Depression Inventory [34] has been widely used in the general population to screen for depression.

#### The General Practice Assessment Questionnaire

The General Practice Assessment Questionnaire (GPAQ) will be used to ascertain the patients' support persons' satisfaction with their care from their GP over the previous 12 months. The GPAQ is very widely used in the UK as part of the GP quality outcomes framework, and has been shown to be acceptable, reliable and have an interpretable factor structure [35].

#### Activities of Daily Living (ADL)

The Lawton and Brody ADL Questionnaire [36] will be used to measure the functional abilities of patients who score in the dementia range on the CAMCOG instrument. This 13-item questionnaire designed for use in elderly patients with neurological disorders, measures both instrumental (eg ability to manage finances, medications) and basic (eg toileting, grooming) ADL. It will be completed by the support person (if available) or the patient.

### Data collection

#### Patient assessment

The research nurse will use a laptop computer to collect demographic data from all consenting patients and to administer the GPGOG, CAMCOG, GDS, WHOQOL-BREF, GPAQ and ADL (for patients in CAMCOG dementia range only). Patients will be asked about any memory-related services accessed, referral to Alzheimer's Australia, and referral to a specialist for memory problems. The research nurse will compile a list of all prescription and over the counter medications currently used by the patient, so that medication can be excluded as a cause of cognitive impairment. Complementary and alternative medicines will be included. In addition the nurse will perform a "75 + Health Assessment" rebateable under the Australian Medicare system on eligible patients where this has been requested by the GP. These data will not be used by the study, but are returned to the GP for his or her use. This part of the assessment is a provided as a service to the GP. Brief questions used in our previous research will be used to measure the acceptability of the interview process. We will ask patients to send answers back in a reply-paid envelope, to avoid bias due to the presence of the nurse. At the completion of the assessment the nurse will hand the patient a sealed envelope. In the case of patients in the intervention group, it will direct the patient to obtain an appointment with his/her GP as soon as possible to follow up on the 75+ Health Assessment and to have the GPCOG re-administered. In the case of patients in the waitlist group, it will suggest a follow up for the 75 Plus Health Assessment only. Patients will be reassessed using the same instruments at 12 and 24 months after baseline interviews.

#### Support person assessment

The research nurse will use a laptop computer to collect demographic data from consenting support persons and to administer the WHOQOL-BREF, BDI and GPAQ.

Information regarding services accessed and acceptability of the interview process will be collected as described above for patients. Patients will be reassessed using the same instruments at 12 and 24 months after baseline interviews.

#### GP audit

GPs will be sent a list of their participating patients by fax or email. They will be asked to confirm each patient's eligibility for the study and to provide their clinical judgement in relation to each patient's dementia status using one of four options: No Dementia, Possible Dementia, Probable Dementia or Definite Dementia. GPs will be asked to complete a supplementary audit for any patients with possible, probable or definite dementia to gather data on differential diagnosis (e.g depression), memory-related tests and investigations performed (i.e. paper and pencil test; pathology; radiology) and referrals to services and specialists. GPs will return their completed audit forms to local project officer via mail, fax or email. GPs will complete audits at baseline, 12 and 24 months.

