### The intervention

All GPs will audit their consenting patients for dementia, and complete a supplementary audit indicating diagnostic evaluation and management for patients they consider to have dementia. This will occur at three time points during the study: baseline, 12 months and 24 months. Intervention GPs will receive education as described below. The rationale for the educational intervention is described in the *Background *section above.

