#### Do GPs trained in screening and management distinguish dementia from other conditions, particularly depression, compared with a waitlist group?

Differential diagnoses (particularly of depression), of the Intervention group will be compared with those of the Waitlist group. Misclassification rates of the GPs in the Intervention group will be compared with those in the waitlist group.

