#### Do GPs trained in screening and management adhere to the guidelines?

Outcomes measured will include identification of reversible causes of dementia, tests ordered and referral patterns to specialists, support services and Alzheimer's Australia, as suggested in the guidelines.

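### At 12 and 24 months, the GP's differential diagnosis, tests and referrals are recorded only for patients the GP rates as possibly having dementia or worse, a rating the intervention aims to change

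*Protocol article*

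**What the plan says.** In the *GP audit* section, GPs confirm each participating patient's eligibility and "provide their clinical judgement in relation to each patient's dementia status using one of four options", one of which is No Dementia. A second form is conditional on that answer: "GPs will be asked to complete a supplementary audit for any patients with possible, probable or definite dementia". Its purpose is "to gather data on differential diagnosis (e.g depression), memory-related tests and investigations performed", together with referrals to services and specialists. *The intervention* section gives the same trigger in other words: GPs "complete a supplementary audit indicating diagnostic evaluation and management for patients they consider to have dementia". Both statements make the GP's own judgement the trigger, not the CAMCOG.

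The analysis section then compares the arms on these items. For aim 1(ii), "Differential diagnoses (particularly of depression), of the Intervention group will be compared with those of the Waitlist group". For guideline adherence, "Outcomes measured will include identification of reversible causes of dementia, tests ordered and referral patterns to specialists". No denominator is given for either comparison.

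Referrals have a second source. In *Patient assessment*, "Patients will be asked about any memory-related services accessed, referral to Alzheimer's Australia, and referral to a specialist for memory problems", whatever the GP has ticked, and "Patients will be reassessed using the same instruments at 12 and 24 months after baseline interviews".

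**The concern.** Aim 1(i) is that trained GPs identify dementia better. If the education works, intervention GPs will tick possible, probable or definite for different patients than waitlist GPs do. Those ticks decide who has a supplementary audit. At 12 and 24 months the patients with data are therefore selected after randomisation by something the intervention is meant to move, and randomisation no longer protects a comparison within that set.

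There is also a gap specific to aim 1(ii), the distinction between dementia and other conditions such as depression. A GP who investigates a patient, concludes depression and ticks No Dementia has made exactly the distinction the aim is about. The form then records neither the alternative diagnosis nor the tests behind it. For GP-recorded differential diagnosis and tests the article describes no other source.

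At stake are secondary outcomes 4 (differential diagnosis), 5 (reversible causes) and the GP-reported part of 6 (referrals).

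**Working it through.** The plan states no figure on this point, so there is none to reproduce. The check has two parts.

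**1. Where each item comes from**

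| Item | Source described | Depends on the GP's label? |
|---|---|---|
| Dementia rating, including No Dementia | Main audit, every listed patient | No |
| Misclassification against the CAMCOG | Main audit and nurse interview | No |
| GP differential diagnosis | Supplementary audit | Yes |
| Tests and investigations | Supplementary audit | Yes |
| Referrals reported by the GP | Supplementary audit | Yes |
| Referrals and services reported by the patient | Nurse interview | No |
| Medication as a reversible cause | Nurse's medication list | No |
| Patient WHOQOL-BREF and GDS (primary) | Nurse interview | No |

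**2. What selection on the label can do**

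Every input here is an assumption; none is in the article.

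- Among CAMCOG-range patients, 60% are mild and 40% more severe.
- True work-up probability is 0.20 (mild) and 0.60 (severe) in both arms, and within each severity level does not depend on the label.
- GPs label 70% of severe cases in both arms. They label 30% of mild cases in waitlist and 60% in intervention.

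True rate in each arm: 0.6 × 0.20 + 0.4 × 0.60 = 0.36. There is no effect.

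Waitlist:
- Labelled share: 0.6 × 0.3 + 0.4 × 0.7 = 0.18 + 0.28 = 0.46
- Labelled and worked up: 0.18 × 0.20 + 0.28 × 0.60 = 0.036 + 0.168 = 0.204
- Rate among labelled: 0.204 / 0.46 = 0.443

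Intervention:
- Labelled share: 0.6 × 0.6 + 0.4 × 0.7 = 0.36 + 0.28 = 0.64
- Labelled and worked up: 0.36 × 0.20 + 0.28 × 0.60 = 0.072 + 0.168 = 0.240
- Rate among labelled: 0.240 / 0.64 = 0.375

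| Denominator | Waitlist | Intervention | Difference | Truth |
|---|---|---|---|---|
| Labelled patients | 0.443 | 0.375 | −0.068 | 0 |
| All CAMCOG-range, unlabelled counted as no | 0.204 | 0.240 | +0.036 | 0 |

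As labelling of mild cases runs from 20% to 80%, the rate among labelled patients falls from 0.48 to 0.35. The recorded rate per CAMCOG-range patient rises from 0.19 to 0.26. The true rate stays at 0.36.

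A contrasting set of assumptions gives the opposite lesson about denominators. Suppose waitlist GPs label 40% and intervention GPs 60%, referral is 60% in the readily recognised 40% and 30% in the extra 20%, and no unlabelled patient is referred. Among labelled patients the rates are 0.60 v (0.40 × 0.60 + 0.20 × 0.30) / 0.60 = 0.50. Over all CAMCOG-range patients they are 0.24 v 0.30, and this is now the true comparison, but only because zero referral was assumed in the unlabelled. Which denominator misleads thus depends on work-up in unlabelled patients, which the audit does not record.

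**The case against.** The strongest reply is that this is a condensed article. It never says the comparisons are made among labelled patients, and a denominator is commonly left to the full protocol or analysis plan. That is fair as to the denominator, and it means no particular bias can be attributed to the plan. It does not answer the point about data collection: the trigger for the form is stated twice, and no analysis plan can recover alternative diagnoses or tests that were never recorded.

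Several stronger readings are tempting, and the article does not support them:

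- *All referral data are restricted to labelled patients.* Only the GP's report is. The nurse asks patients about referrals and services, with repeats at 12 and 24 months.
- *Correct No Dementia decisions are never captured.* The rating is recorded for every patient and can be checked against the CAMCOG. What is lost is the reason and the work-up behind it.
- *Aim 1(ii) cannot be answered.* Differentials are recorded for patients rated possible dementia, misclassification can be compared by arm, and the GDS is given to patients at each assessment. One can therefore ask whether GPs call depressed patients demented. The aim is incompletely measured, not out of reach.
- *The baseline data are affected too.* The first education visit follows the baseline audit, so education cannot have shaped those labels.
- *The arm comparisons are shown to be biased, by so many points.* Size and direction depend on how far labelling differs by arm and on the denominator; neither is in the article.

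**Conclusion.** The concern holds in a limited form. At the 12- and 24-month audits, GP-recorded differential diagnosis, tests and GP-reported referrals exist only for patients selected by a judgement that the intervention targets. Arm comparisons of these items are liable to selection bias whose size and direction cannot be determined from the article. On the assumed no-effect inputs it was about 7 points against the intervention with one denominator and about 4 points in its favour with the other. These figures show the mechanism and are not estimates for this trial.

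The consequence is confined to secondary outcomes. The patient WHOQOL-BREF and GDS, detection and misclassification against the CAMCOG, and patient-reported referrals stand as planned. The point is worth acting on because a stated aim and the guideline-adherence question rest on the affected data.

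**What to change.** In both arms, at the 12- and 24-month audits, do one of the following.

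1. Add two brief items for every listed patient: cognitive symptoms attributed to depression or another cause (yes/no), and memory-related tests done (yes/no). The tests item should count the study's own GPCOG separately, since intervention GPs administer it by design.
2. Or require the supplementary items for a set defined without the GP's label, such as all patients in the CAMCOG dementia range or with a raised GDS. Both are measured by interviewers blind to allocation. The GDS cut-off must be fixed in advance. Baseline values are preferable, because the follow-up GDS is a primary outcome that the intervention may itself change. A CAMCOG-only set would miss depressed patients who score outside the dementia range.

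Compare the arms within that label-independent set. Make the patient-reported referral and service data the main referral comparison, with GP-reported referrals as supporting detail. Do not count unlabelled patients as not worked up where nothing was recorded; the second row of the no-effect table shows the bias this can create.

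The cost is a slightly longer audit, some prompting of waitlist GPs to think about other causes, and no baseline counterpart for the new items. The referral comparison needs no new data, though self-report by cognitively impaired patients may be incomplete. The services information already collected from support persons can help there.

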### Outcome measures

Primary outcome measures related to the first aim (collected at baseline, 12 months and 24 months) are:

1. World Health Organization Quality of Life-Bref Scale (WHOQOL-BREF) score for patients

2. Geriatric Depression Scale score for patients

Secondary outcome measures related to the first aim (collected at baseline, 12 months and 24 months) are:

1. World Health Organization Quality of Life-Bref Scale (WHOQOL BREF) for carers

2. Beck Depression Inventory score for carers

3. Agreement of GP audit for dementia with CAMCOG instrument

4. GP differential diagnosis for dementia

5. GP identification and treatment of reversible causes of dementia 6.GP dementia related referrals made

7. General Practice Assessment Questionnaire score

8. Acceptability of the process scale score

9. Services accessed

To meet the second aim of the study, screening and case finding groups (as defined above) will be compared on primary and secondary outcome measures 1 and 2 as listed above. The GPCOG score will be compared with the gold standard of the CAMCOG score to address the third aim of the study. The performance of the GPCOG against the CAMCOG will also be compared with that of the MMSE against the CAMCOG, as the MMSE is widely used to screen for dementia.

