### Sample size

It was calculated that 45 patients with dementia in each group (Waitlist and Intervention) would give a power of 0.9 to detect a 7% difference between the change in pre and post scores on any of the four domain scales of the WHOQOL-BREF with a type 1 error of .05. The population standard deviation used is 18.5 [32] and the Pearson correlation coefficient between the pre and post scores for both groups is assumed to be 0.7, based on pilot data available from the University of Melbourne.

The hierarchical nature of the study design will probably lead to some within cluster correlations and the greatest impact of this is likely to be associated with patients clustered within a GP practice. Clustering within each GP may be discounted, as it is anticipated that most GPs will have less than five patients with dementia in this study. Assuming an intra-class correlation coefficient of 0.05 and an average cluster size of 5 patients with dementia in a practice, this gives a design effect of 1.45 and a total sample size of 54 patients per group. We will therefore allow for 56 patients with dementia in the waitlist group and 112 in the intervention group to allow for comparison of outcomes between the waitlist and intervention groups overall. This sample size also allows comparison of "case finding" and "screening" patients and their support persons within the group. It is assumed that about 50% of participants will be screening and 50% case finding. Thus, we aim to recruit 168 participants with dementia overall. Based on a dementia prevalence of approximately 10% in over 75 year old Australians [37], we aim to recruit a total of 2,000 participants.

For the GDS, following the same set of assumptions and approach as for the WHO QOL-BREF (power, type 1 error and correlations), 45 patients in both the Intervention and Waitlist groups would allow detection of an average difference in the change in pre and post scores of 0.9 points on the 15 point GDS, using a standard deviation of 2.39 [28]. The cluster effect would be the same as for the WHOQOL-BREF.

For an estimate of test re-test reliability on the GPCOG a sample size of 100 will be used to ensure the correlation is estimated to a reasonable precision. The 95% confidence interval for a Pearson correlation of 0.9 would be [0.86, 0.93] and for a correlation of 0.80 [0.73, 0.85].

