### Study drop outs/withdrawals

#### Subjects

We aim to recruit 2000 subjects, based on a dementia prevalence rate of 10% in the Australian population aged 75 years and over [37]. We anticipate a 10% drop out per annum, giving us 180 subjects with dementia at the 12 month mark, and 162 at 24 months, with a small number of incident cases.

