### Statistical analyses

All surveys collected on laptop computers will be downloaded to a central database. Where necessary in the analysis, the longitudinal and hierarchical/cluster nature of the study design will be taken into account using mixed effects models and other appropriate methods (see below). The primary analysis will be by intention to treat. Analyses will address the following questions:

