#### Do GPs trained in screening and management provide better health outcomes?

Outcomes of Intervention and Waitlist groups will be compared at twelve months, for both patients and their carers (quality of life, depression, satisfaction with care, services accessed)

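### The primary outcomes are set for patients without restriction, but sample size and power are worked out only for patients with dementia

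*Protocol article*

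**What the plan says.** Under Outcome measures, the primary outcomes for the first aim are the "World Health Organization Quality of Life-Bref Scale (WHOQOL-BREF) score for patients" and the "Geriatric Depression Scale score for patients". Neither is limited to dementia. Under Statistical analyses, "The primary analysis will be by intention to treat", and the question on health outcomes is answered thus: "Outcomes of Intervention and Waitlist groups will be compared at twelve months, for both patients and their carers". No dementia subset is named there either.

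Under Patient assessment, all consenting patients receive the GDS and the WHOQOL-BREF. The one instrument in that list restricted to the CAMCOG dementia range is the ADL questionnaire.

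The Sample size section works with a different group: "45 patients with dementia in each group (Waitlist and Intervention) would give a power of 0.9". It then plans for 56 waitlist and 112 intervention patients with dementia and says that these numbers serve the comparison of the two arms. The total of 2,000 follows from a prevalence of about 10%. The section on drop-outs also counts subjects with dementia: 180 at 12 months and "162 at 24 months, with a small number of incident cases".

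**The concern.** The outcome and analysis sections, followed as written, put about 2,000 patients into the primary comparison. The sample size section puts 168 into it. These are different estimands with different power.

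If the larger set is analysed, most of the patients are people for whom an effect of dementia identification and management is uncertain, and the planned effect size was not set for them. If the smaller set is meant, the article does not say which label defines it. It offers the CAMCOG dementia range (used to recruit support persons), a DSM diagnosis derived from the CAMCOG (used for the GPCOG test parameters) and the GP's audit judgement. The intervention is designed to change the last of these. While the population and its definition stay open, the primary result depends on a choice that could still be made once data are in hand.

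Patients who first enter the dementia range at 12 or 24 months are a related issue. They are classified after exposure to the allocated arm, so whether they enter the set could depend on the arm.

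**Working it through.** **Inputs from the Sample size section:** difference in change 7% (taken as 7 points on a 0–100 domain scale); SD 18.5; pre-post correlation 0.7; type 1 error 0.05 (taken as two-sided); ICC 0.05; 5 patients with dementia per practice; prevalence 10%; GDS difference 0.9 with SD 2.39. **From other sections:** 2:1 allocation; 10% drop-out per year.

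**1. The article's own figure.** SD of change = 18.5 × √(2 × (1 − 0.7)) = 14.33. For 45 vs 45, SE = 14.33 × √(2/45) = 3.02 and 7/3.02 = 2.32, so power is about 0.64. For the GDS, the SD of change is 2.39 × √0.6 = 1.85, and power is again about 0.64. Power of 0.9 needs 2 × (14.33 × 3.2416/7)² = 88.1, that is 89 per group. Without the factor 2 the same formula gives 44.0 (GDS 44.5), which rounds up to the stated 45. So 0.9 is not reproduced even in patients with dementia.

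**2. Patients with dementia at the planned 56 vs 112.** SE = 14.33 × √(1/56 + 1/112) = 2.35. Power is 0.85 without clustering, 0.78 at a design effect of 1.20 and 0.70 at 1.45. The article states 1.45, but its ICC and cluster size give 1 + 4 × 0.05 = 1.20, and its 54 per group equals 45 × 1.20.

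**3. All patients.** Let s be the effect in patients without dementia as a share of the effect in patients with dementia. The documents give no value for s, so a range is shown. Mean effect = 7 × (0.10 + 0.90 × s). The same SD and correlation are assumed for everyone.

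- Recruited: 667 vs 1,333, SE = 14.33 × √(1/667 + 1/1,333) = 0.68.
- At 12 months after 10% drop-out: 600 vs 1,200, SE = 14.33 × √(1/600 + 1/1,200) = 0.717.
- Design effect 3.45 = 1 + 49 × 0.05. It assumes 50 patients per practice, inferred from 5 with dementia at 10% prevalence, and the same ICC.

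| s | Mean effect | 667 vs 1,333: no clustering / 3.45 | 600 vs 1,200: no clustering / 3.45 |
|---|---|---|---|
| 0 | 0.70 | 0.18 / 0.08 | 0.16 / 0.08 |
| 0.10 | 1.33 | 0.50 / 0.18 | 0.46 / 0.17 |
| 0.25 | 2.28 | 0.92 / 0.44 | 0.89 / 0.40 |
| 0.50 | 3.85 | >0.99 / 0.86 | >0.99 / 0.82 |

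GDS results at 667 vs 1,333 agree within 0.01. Practices may be smaller: 2,000/160 GPs is 12.5 patients per GP. With one GP per practice the design effect is 1 + 11.5 × 0.05 = 1.575, and power at s = 0 with 600 vs 1,200 is about 0.12.

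**The case against.** The strongest reply is that the article never says all patients. The Sample size section ties the arm comparison to patients with dementia, retention is counted in them, and support persons are recruited only for patients in the CAMCOG dementia range. Intention to treat means analysis by allocated arm and does not by itself widen the population. A condensed article may also leave the exact analysis set to a fuller document. Much of this stands: dementia is the likelier intention, and the article cannot be said to define the outcomes for everyone. It does not remove the inconsistency. The outcome and analysis sections carry no restriction, although the article states one for the ADL questionnaire.

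A reader might infer that the analysis as written dilutes any effect tenfold. The documents do not support that. Tenfold needs zero effect in patients without dementia, which is nowhere stated. The aims include telling dementia from depression and eliminating reversible causes of cognitive impairment, and every intervention patient is sent back to the GP, so some effect is plausible. At s = 0.25 the dilution is 7/2.28 = 3.1-fold. Even at s = 0 the sample is ten times larger, so signal-to-noise falls by about √10 = 3.2 before clustering.

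A reader might also infer that 0.9 is the true power in patients with dementia. It was calculated for them, but it does not follow from the inputs.

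On incident cases, the drop-out section gives a headcount and does not define an analysis set. Baseline CAMCOG status may itself be obtained after a practice is allocated, since allocation follows GP consent. What protects a baseline set is therefore blinded assessment before the intervention, and not timing before randomisation.

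**Conclusion.** The point holds as an inconsistency about who is in the primary analysis. The power statement belongs to patients with dementia and cannot be read across to an all-patient comparison. There, power could be anywhere from 0.08 to above 0.99, depending on the unstated effect in patients without dementia and on clustering. The value of 0.08 is the unfavourable corner (no effect in the other 90%, 50 patients per practice, ICC 0.05) and is not a forecast.

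Naming the dementia population settles the inconsistency but does not restore 0.9. On the article's inputs, 56 vs 112 gives 0.78 at a design effect of 1.20 and 0.70 at 1.45.

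These results assume that 7% means 7 points, a two-sided test on change scores, and the same SD and correlation in patients with and without dementia. With baseline adjustment (ANCOVA) the figures rise somewhat: 0.71 for 45 vs 45, and 0.84 or 0.77 for 56 vs 112 at the two design effects. Nothing in the article suggests that the population will be chosen from the results. The text simply does not rule it out.

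**What to change.** - Under Outcome measures and under the analysis question on health outcomes, state that the primary WHOQOL-BREF and GDS comparison is in patients who score in the CAMCOG dementia range at the blinded baseline interview, analysed by allocated arm. Say explicitly that this interview precedes the intervention.
- Report patients who first enter the range at 12 or 24 months separately.
- Make the all-patient comparison secondary.
- Restate the power for the named population, with the two-group formula, the 2:1 allocation and a design effect that agrees with the stated ICC and cluster size.

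The cost is a few sentences and a recalculation. No new data are needed, because every consenting patient already has the CAMCOG. The downsides are that a few incident cases leave the primary set and that the stated power becomes less favourable. At 12 months, the time point of the comparison, the article expects 180 patients with dementia against a target of 168, so leaving incident cases out does not threaten that target.
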